## Abstract

**Background:**

Staff currently working in long-term care experience several difficulties. Shortage of staff and poor working conditions are amongst the most prominent, which pose a threat to staff’s sustainable employability. To improve their sustainable employability it is important to create working conditions that fulfil workers’ basic psychological need for autonomy, relatedness and competence in line with Self-Determination Theory. Since many long-term care organisations work with self-managing teams, challenges exist at team level. Therefore, there is a need to implement an intervention aimed at maintaining and improving the sustainable employability of staff on team level.

**Methods:**

We developed a participatory workplace intervention, the Healthy Working Approach. In this intervention teams will uncover what problems they face related to autonomy, relatedness and competence in their team, come up with solutions for those problems and evaluate the effects of these solutions. We will evaluate this intervention by means of a two-arm randomized controlled trial with a follow-up of one year. One arm includes the intervention group and one includes the waitlist control group, each consisting of about 100 participants. The primary outcome is need for recovery as proxy for sustainable employability. Intervention effects will be analysed by linear mixed model analyses. A process evaluation with key figures will provide insight into barriers and facilitators of the intervention implementation. The Ethical Committee Social Sciences of the Radboud University approved the study.

**Discussion:**

This study will provide insight in both the effectiveness, and the barriers/facilitators of the implementation process of the Healthy Working Approach. The approach is co-created with long-term care workers, focuses on team-specific challenges, and is rooted in the evidence-based participatory workplace approach and Self-Determination Theory. First results are expected in 2022.

**Trial registration:**

Netherlands Trial Register, NL9627. Registered 29 July 2021 - Retrospectively registered.

## Background

Sustainable employability of the workforce is a growing concern for many sectors, but especially for long-term care. On the one hand, the aging population requires more long-term care, whereas on the other hand the number of caregivers relative to older adults is declining. It appears difficult to attract new personnel while retaining current staff, especially for the direct care workers like nurses and personal care workers [1]. The direct care workforce currently working in long-term care experience several difficulties at work like shortage of staff, high physical and emotional demands, heavy workload, scheduling challenges, insufficient supervision and limited training and career advancement prospects which relate to job dissatisfaction and high turnover [2–7]. With many employees leaving their current profession, the burden increases for those who remain, which poses a threat to long-term care workers’ sustainable employability [1, 8–12].

Many scholars argue that in order to improve sustainable employability of current staff, the focus should be on improving working conditions and job quality [1, 13]. This is in line with needs expressed by long-term care workers for reducing job demands (e.g. reducing workload, diminishing rules and regulations) and improving job resources (e.g. more autonomy, appreciation and training possibilities) [14]. Having too many job demands and too little job resources to buffer against those demands, is known to have a negative impact on employee health and organisational outcomes [15]. Having too high job demands is not only energy depleting in itself, but also frustrates employees in the fulfilment of their basic psychological needs for autonomy, relatedness and competence [16]. According to the Self-Determination Theory precisely those three basic psychological needs are required for humans to actualize their potential [17]. *Autonomy* is experienced when people act from their own interests and values, and feel as if their behaviour is an expression of themselves [18]. *Relatedness* involves the feeling of being connected and belonging to others and to experience a sense of communion [18]. *Competence* refers to feeling effective in social interactions and experiencing opportunities to practice and express ones capabilities [18]. Satisfaction of these three basic needs relates to a variety of beneficial outcomes for employees, which ultimately benefit their sustainable employability [16, 19–21]. It is therefore important to foster the satisfaction of the needs for autonomy, relatedness and competence for employees to thrive at work [16].

In long-term care, many organisations have chosen an organisational structure that empowers its staff by working with self-managing or self-directing teams. Self-managing teams are autonomous teams, where the responsibility for providing good quality care and optimizing the wellbeing of the resident lies within the team instead of with a supervisor or team leader. The teams can decide on a range of tasks such as rostering, planning, individual and team performance monitoring, professional development and care delivery [1]. In self-managing teams different types of professionals (e.g., nurses, nursing assistants, social workers, therapists) work together to realise good quality of care for the residents. Long-term care teams in our paper therefore refer to a group of professionals responsible for accommodating care and assistance to a number of physically and/or cognitively impaired, typically older, people. As teams and residents vary, there is considerable variation in how self-managing teams organize the care for their residents [22]. Consequently, challenges with regards to the organisation of work likely differ between teams. Therefore, team level interventions are preferred over individual level interventions to obtain a sustainable long-term care workforce [23]. Moreover, given the diversity between teams within long-term care facilities, a one size fits all (teams) approach is not likely to be effective in protecting and stimulating sustainable employability [24, 25]. For the purpose of this study, we developed the Healthy Working Approach in close collaboration with long-term care workers. The Healthy Working Approach consists of a participatory workplace intervention at team level. The participatory approach is an established method aimed at promoting health and safety at work by means of a number of defined process steps, guided by a facilitator. The aim of these steps is to identify the most important bottlenecks at work and to come up with appropriate solutions using a concrete plan of action and equal input from all stakeholders [26]. This approach likely results in high degree of acceptance of proposed changes, which increases the likelihood that new way(s) of working implemented based on the intervention will be sustained over time [27, 28]. A participatory workplace intervention appears to be effective in improving several health issues, like hand eczema and back pain at the organisational level in various health settings [29–31]. In our Healthy Working Approach we used the Self-Determination Theory as the foundation for the focus of the participatory workplace intervention. The aim of our Healthy Working Approach is therefore to improve sustained employability of long-term care workers through improving fulfilment of their basic psychological needs at work. To gain insight into the effectiveness of the intervention, we will evaluate both the process of the Healthy Working Approach and the effects on sustainable employability in long-term care organisations working with self-managing teams. The primary outcome is need for recovery, also referred to as fatigue after work, as proxy for sustainable employability. Need for recovery is known to be a precursor for health problems that have a strong negative effect on the health and well-being of employees [32–35]. Moderate and high levels of burnout for example are highly prevalent in long-term care workers and are a long-term effect of short-term desires to be relieved from work demands in order to restore (also known as need for recovery) [36, 37]. Prolonged and increased need for recovery can therefore be seen as an early sign of a decreasing sustainable employability.

The main research question is:

What are the effects of the Healthy Working Approach on the sustainable employability of long-term care workers over a one year follow-up?

The main objectives of this study are:To gain insight into the effectiveness of the Healthy Working Approach on need for recovery in long-term care workers over one year;To gain insight into the process of implementing the Healthy Working Approach in long-term care teams.

## Methods

### Study Design

This is a randomised controlled trial with an intervention group and waitlist control group. There will be four measurement moments: at baseline (T0), 6 months (T6), 9 months (T9) and 12 months after baseline (T12). Data collection started in May 2021. The study protocol was approved by the Ethical Committee Social Sciences of the Radboud University (number: ECSW-2021-012).

### Setting

This study will be conducted in long-term care organisations that work with self-managing teams in the Netherlands.

### Procedure

Long-term care organisations are invited to participate in the study. After permission has been obtained, care teams are invited to participate via internal communication tools (e.g., intranet), and a personal e-mail with a link to the baseline questionnaire (T0). The questionnaire starts with an eligibility check followed by a digital informed consent. After participants have given their consent and their contact details, they are redirected to the main questionnaire. Information and questionnaires are also available in print. To enhance the response rate, the researcher will contact the teams to ask them how the research team can support them in filling out the questionnaires, for example by visiting with a laptop, or by bringing over hardcopy questionnaires. Recruitment of participants will continue until target sample size is reached.

### Participants

All professionals who both directly and indirectly contribute to providing good quality of care to residents in long-term can participate in the study. The eligibility check in the first questionnaire verifies whether the individual meets the following inclusion criteria:The long-term care worker is able to read and understand the Dutch language;The long-term care worker is minimally 18 years old.

Long-term care workers are excluded from participation when meeting the following exclusion criteria:The long-term care worker is on sick leave for one month or more before completing the baseline questionnaire;The employment contract of the long-term care worker ends within six months after completing the baseline questionnaire.

Because the intervention is at team level, teams are included in the study if at least a third of the team members have completed the baseline questionnaire and at least three team members are willing to represent their team in the three meetings of the intervention (i.e. take part in the working group).

### Participant involvement

Long-term care workers are involved in the design of the Healthy Working Approach by means of interviews in which their needs regarding sustainable employability are explored. Their needs formed the basis for the development of the Healthy Working Approach, which we presented to several teams/team members in order to check the feasibility and acceptability of the intervention. Key persons involved in healthy working within the long-term care organisation are involved in designing the recruitment process of facilitators and participating teams as well as in an appropriate dissemination plan for the facility. Outcomes are chosen based on interviews with employees and key figures within the long-term care organisation.

### Intervention: the Healthy Working Approach

The intervention consists per team of three meetings of one hour each led by a facilitator, who is a trained employee from within the long-term care organisation. Teams choose at least three representatives of their team to take part in a working group that will attend the meetings. The working group is responsible for representing the entire team and for reporting back to the team. The approach aims to result in improvements that benefit the whole team.

#### Meeting 1: Problem analysis (± one month after baseline)

In the first meeting, the working group starts with a brainstorm about problems within their team related to healthy working in the context of the three basic psychological needs, namely autonomy, relatedness and competence. Next, the working group starts prioritizing and chooses two or three problems that have great impact (high severity and frequency) for the entire team. The working group reports the chosen problems to the entire team, to make sure that everyone agrees these are problems that need to be tackled within their team. The facilitator ensures a safe and confidential environment, where everyone and every opinion is equal and respected.

#### Meeting 2: Solutions & action plan (one to two weeks after meeting 1)

After two or three problems that are agreed upon by the whole team, the working group brainstorms about solutions for these problems in the second meeting. The brainstorm about solutions starts broad and may include different sorts of solutions (technical or organisational solutions, working conditions or support). Potential solutions are prioritized based on criteria simplicity, feasibility, support, practicability and expected effectiveness. The working group formulates an implementation plan for the best one or two solutions for each problem. The plan includes specific, measurable, achievable, relevant and timebound (SMART) actions. The working group reports the solutions back to the entire team, to make sure that everyone knows which actions are agreed upon and what is expected from them.

#### Meeting 3: Implementation and evaluation (one to two months after meeting 2)

In the implementation phase, teams are guided and supported by the facilitator where necessary in carrying out the solutions. In the third meeting, the implementation status of the solutions are discussed (implemented, not implemented, in progress). If needed, solutions or additional steps will be discussed to improve the implementation status of solutions.

### Allocation of intervention and waitlist control group

Randomisation will take place at team level. The randomisation is performed by a research assistant who has no knowledge about the teams, using randomizer.org. In this tool, teams are inserted as pairs: of each pair one team is assigned to the intervention group and the other to the control group. The waitlist control group will start the intervention after completing the 12-month follow-up questionnaire. The intervention and control groups are aware of their own allocation status, but not of the allocation status of other teams. The allocation status of teams are known to the researchers involved in this study. In case of close collaboration between multiple teams within a department, the department is randomised to avoid contamination between these teams.

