### Outcomes

#### Primary outcome

*Need for Recovery* will be measured with the 11 dichotomous items (0 *no* or 1 *yes*) of the Questionnaire on Psychosocial Job Demands and Job Stress [38]. The need for recovery score is a percentage score (0 to 100) of positive answers on the items. Higher scores indicate a higher degree of need for recovery after work. The scale has shown to possess good psychometric qualities in terms of (content) validity and internal consistency (Cronbach’s alpha ranging from .83 to .92) [39].

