### Data management and analysis

Before the start of the project, all issues of data management will be addressed in a data management plan. For this, Radboud University has a tool, that includes feedback from Research Data Management (RDM) Support. Training and support in writing a data management plan are offered by the section RDM Support and the data steward of the institute. In order to check whether the research has been carried out properly and reliably, authorised persons within the Behavioural Science Institute or Radboud University and (inter)national supervisory authorities (for example, the Netherlands Authority for the Protection of Personal Data) are able to inspect the data. While research is ongoing, data will be stored on the Radboud University’s network. The server space allows for managed access to and the sharing of data between and among partners and guests during the project. Safe and secure storage of data is guaranteed by the Information Technology security and safety protocols of the campus network.

We will perform descriptive analyses (means, standard deviation, frequencies) on all outcomes and covariates. For the main analysis, we will perform linear mixed model analyses with need for recovery as primary outcome, and group (intervention/control) x time interaction as independent variable, taking into account potential confounding prognostic factors. Potential confounders are included in the model when they account for at least 10% change in the main effect size of the group x time interaction. We will take into account nesting of the data. Similar analyses will be done with the secondary outcome measures.

Main analyses are performed according to the “intention to treat” principle and the unit of analysis is on the individual level. In addition, we will perform a per-protocol analysis to take into account teams in the intervention group that did not participate in the intervention or did not implement the intervention as planned. Any cases of missing data will be dealt with by imputation.

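### Researchers know every team's allocation while covariates are chosen by their effect on the estimate and no masking is stated, which leaves an avoidable risk of analyst bias

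*Protocol article*

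**What the plan says.** All places are in the Methods of the protocol article.

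- *Allocation of intervention and waitlist control group*: "The randomisation is performed by a research assistant who has no knowledge about the teams, using randomizer.org". On participants: "The intervention and control groups are aware of their own allocation status, but not of the allocation status of other teams". On the research group: "The allocation status of teams are known to the researchers involved in this study".
- *Primary outcome*: need for recovery is the percentage of positive answers to 11 yes/no items completed by the worker.
- *Data management and analysis*: the main analysis is a linear mixed model with a group-by-time interaction, by intention to treat. On covariates: "Potential confounders are included in the model when they account for at least 10% change in the main effect size". A per-protocol analysis is added to deal with "teams in the intervention group that did not participate in the intervention or did not implement the intervention as planned".
- *Procedure*: to raise response, "the researcher will contact the teams to ask them how the research team can support them in filling out the questionnaires". The two examples given there are practical ones: a laptop visit and delivery of paper forms.
- *Participant time line*: teams reaching 75% response at follow-up are offered a gift, with no distinction by arm.
- *Process evaluation*, Table 1: intervention participants answer extra questions within the 6- and 9-month questionnaires.

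**The concern.** Participants cannot practicably be blinded in a waitlist design with a self-reported outcome. What remains available is to keep the analysis, and any contact at follow-up, independent of the arm. The article states that the researchers know the arms and makes no exception for whoever analyses the data.

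Two analysis steps make this matter. The covariate rule is driven by the treatment estimate itself, so the adjusted model cannot be known until follow-up outcomes have been analysed by arm. The per-protocol set depends on a judgement about implementation. Someone who knows the arms and has seen the outcomes can tell which way each choice moves the result. Even if nobody acts on that knowledge, the trial could not show it. At stake is the credibility of the main effect estimate and of the per-protocol result reported beside it.

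**Working it through.** The plan gives no figure on this point to reproduce. The check sets the passages side by side and then sizes the mechanism under stated assumptions.

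**1. Where discretion can enter.** *Prognostic factors* lists ten candidates: age, gender, education, job title, years employed, contract type, contractual hours, informal care hours, and frequency and total days of sickness absence. Measurements are at T0, T6, T9 and T12. If time is categorical, the group-by-time term has three coefficients (T6, T9 and T12 against T0). The rule as written does not say which of them must move by 10%, or whether candidates are tried singly or in sequence. The threshold is fixed; its application is not fully fixed.

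**2. The 10% rule under no true effect.** Assumptions: 161 people (the plan's analysable number), ten covariates independent of group, joint R² of 0.1 or 0.3, one follow-up, no clustering, each covariate tested singly against the unadjusted estimate, 4,000 runs. Simulation error at 5% is √(0.05 × 0.95 / 4000) = 0.34 percentage points.

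| Model | R² = 0.1 | R² = 0.3 |
|---|---|---|
| Unadjusted | 5.1% | 5.0% |
| 10% rule, applied mechanically | 5.3% | 4.3% |
| All ten covariates | 5.2% | 4.9% |
| Most significant of the three | 7.5% | 8.1% |
| Mean covariates kept by the rule | 4.6 | 6.3 |

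Applied mechanically, the rule does little harm to type I error. It does keep about half of the covariates although none is a true confounder here, because 10% of a near-zero estimate is a very small change. The inflation appears only when someone chooses among models after seeing the results.

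**3. What a small shift between arms would do.** This applies to a shift from any source. Inputs from *Sample size calculation*: SD 29.75, N 161, target difference 12, ICC 0.025. Equal arms are assumed.

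- SE = 29.75 × √(4/161) = 4.69. With an assumed 8 people per team the design effect is 1 + 7 × 0.025 = 1.175, so SE = 4.69 × √1.175 = 5.08.
- Two-sided rejection with no true effect and a shift of b points: 1 − Φ(1.96 − b/SE) + Φ(−1.96 − b/SE).
- b = 2: 7.1% (6.8% with clustering). b = 3: 9.8% (9.1% with clustering).
- For scale, one item is 100/11 = 9.1 points. One item changed in a quarter of one arm would be 9.1/4 = 2.3 points, or 19% of 12. That quarter is an assumption; the documents supply no such figure.

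**4. The collection route.** The support sentence follows the text on the baseline link and consent, and comes just before the statement on how long recruitment continues. *Participants* admits a team only once a third of its members have completed baseline. Help with baseline therefore probably precedes allocation; the timeline figure is not shown, so this is an inference. The plural word for questionnaires leaves use at T6 to T12 possible but unstated. The help described is logistical and addressed to teams in general.

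**The case against.** The strongest case against is that the article openly describes an unblinded trial and already contains safeguards. Randomisation is done by someone with no knowledge of the teams, and teams are not told each other's status. The items and scoring are fixed, so no assessor rates anything. Intention to treat is the main analysis, and the per-protocol analysis is additional and cannot move it. A numerical threshold applied to the same model gives the same covariates whether or not the analyst knows the arms, and the simulation bears this out. Masked coding is ordinary SAP content, and the SAP is not shown.

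Most of this stands. A reader might infer that the trial has no protection against collection or analyst bias; the safeguards just listed rule that out. A reader might also infer that researchers who know the arm help people complete follow-up questionnaires, or chase the arms unequally. The documents do not say so: the support text sits with recruitment and baseline, and the one follow-up retention measure described, the gift, does not differ by arm. Nor does the article say that those who support teams also analyse the data.

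What survives does not depend on an omission. The researchers' knowledge of allocation and the estimate-driven covariate rule are both stated choices. The SAP may add masking, but a covariate set chosen from the treatment estimate is what the article commits to.

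**Conclusion.** The point holds in a limited form. Known allocation, a covariate rule tied to the estimated effect and a judgement-based per-protocol set, with no masking stated, leave a risk of analyst bias that could be removed at little cost. The risk comes from discretion combined with knowledge of the arm, not from the 10% threshold itself.

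The documents do not give the size of any bias. The increase from 5% to 7.5–8.1% shows what free choice among three models would do under the simplified simulation; the plan does not propose such a choice. The 2- and 3-point shifts are likewise assumed. The collection route is conditional: it matters only if questionnaire support is also used at T6 to T12. This is worth changing, but it does not undermine the design.

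**What to change.** 1. Replace the 10% rule with a covariate set chosen from the listed baseline prognostic factors and dated before follow-up outcomes are seen.
2. Write down what counts as implementation for the per-protocol analysis, and fix the team list from process data before outcomes are seen.
3. Run the primary analysis on a file with arms coded A/B, prepared for instance by the assistant who randomised. Hold the intervention-only T6/T9 process questions and the per-protocol fields separately until the main model is final; otherwise they reveal the arm. Replace team identifiers with neutral codes, because the researchers know allocation by team and the model needs a team variable.
4. State whether the questionnaire support applies after baseline. If it does, give both teams of a randomised pair the same reminders and purely logistical help, and let respondents complete the form in private.

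The cost is protocol or SAP wording, some data handling, and less freedom to help one team more than its pair. No new data are needed. Reporting bias from participants who know their arm is not removed and should be acknowledged as a limitation.
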